# Effectiveness of acupuncture for breast cancer related lymphedema: protocol for a single-blind, sham-controlled, randomized, multicenter trial

**DOI:** 10.1186/s12906-017-1980-0

**Published:** 2017-09-21

**Keywords:** Acupuncture, Breast cancer related lymphedema, Protocol, Trial

## Abstract

**Background:**

Although various treatments for breast cancer related lymphedema exist, there is still a need for a more effective and convenient approach. Pilot studies and our clinical observations suggested that acupuncture may be a potential option. This study aims to verify the effectiveness of acupuncture on BCRL and evaluate its safety using a rigorously designed trial.

**Methods/Design:**

Women who are clinically diagnosed as unilateral BCRL, with a 10% to 40% increase in volume compared to the unaffected arm, will be recruited. Following baseline assessment, participants will be randomized to either the real acupuncture group or sham-acupuncture group at a ratio of 1:1, and given a standard real acupuncture or sham-acupuncture treatment accordingly on both arms followed by the same usual care of decongestive therapy. Volume measurements of both arms will be performed for every participant after each treatment. Data collected at baseline and the last session will be used to calculate the primary outcome and secondary outcomes. Other data will be exploited for interim analyses and trial monitoring. The primary outcome is the absolute reduced limb volume ratio. Secondary outcomes are incidence of adverse events and change in quality of life. A t test or non-parameter test will be used to compare the difference between two groups, and assess the overall effectiveness of acupuncture using the SPSS software (version 12).

**Discussion:**

This study will help expand our knowledge about the effectiveness of acupuncture on BCRL, and how acupuncture might be used in the management of this condition. Acupuncture may be a promising complement or alternative to conventional lymphedema treatment methods, if its effectiveness is confirmed.

**Trial registration:**

ClinicalTrials.gov NCT02803736 (Registered on October 31, 2016).

**Electronic supplementary material:**

The online version of this article (10.1186/s12906-017-1980-0) contains supplementary material, which is available to authorized users.

## Background

As a long-term complication stemming from the disruption of lymph flow, breast cancer related lymphedema (BCRL) is a distressing problem afflicting around 20% of women who underwent breast cancer treatment, and is characterized by the chronic swelling of one or both upper extremities [1–4]. Depending on the extent of the surgery and auxiliary treatments, BCRL affects patients differently, and may develop one or several years later after surgery [5]. With the increase in breast-cancer incidence as well as the five-year survival rate, it is estimated that there are approximately 530,000 patients facing BCRL in China only [6]. Since patients under this condition often require lifetime management [7], it imposes a big burden on the society with long-term costs, and makes up a significant source of hardship for many families due to health-related productivity loss [8, 9]. According to research, common risk factors for BCRL includes obesity, axillary lymph node dissection, postoperative radiotherapy, infection, and history of lymphangitis [10, 11]. Moreover, there is no cure for BRCL so far, and the only way is to avoid risk factors, reduce the severity of symptoms and improve the function of the affected arm. As a result, almost every patient experiencing breast cancer surgery is advised to take precautions and take good care of the affected arm to prevent lymphedema [12, 13]. All these things pose a reminder to patients of their malignant status and become a prominent psychosocial problem that afflicts breast cancer survivors [14, 15]. As a result, the quality of life is much lower for patients after breast cancer surgery than those without this condition [16–19]. At present, there are various treatment options to deal with BCRL, including lymph drainage, low-level laser, micro-surgery, and transplantation of axillary lymph nodes [20–24]. However, no consensus has been reached on any specific approach for BCRL [25], and the management of BCRL remains a major challenge for both physicians and patients [26].

In the theory of Traditional Chinese Medicine (TCM), diseases like BCRL are considered as the same “zheng” as “edema” [27], and is thought to be caused by qi deficiency and blood stagnation. Acupuncture, as an ancient therapy in TCM, is thought to have the efficacy to stimulate the transformation of qi and drainage of dampness [28], and is widely used for various diseases including edema in East Asia for thousands of years [29]. Previous researches in patients with lymphedema suggest that this treatment might reduce swelling by improving circulation without inducing safety issues [30–35]. However, results regarding its effectiveness in the reduction of swelling have not yet been well established, and no randomized controlled trial has been performed on this issue. Therefore, with this protocol, we aim to evaluate the effectiveness of acupuncture for the treatment of BCRL.

## Method

### Study setting/design

This multi-center two-arm randomized clinical trial will be performed in the following three medical centers: the Fourth Affiliated Hospital of Guangxi Medical University (about 400 breast cancer patients seen annually), the Third Affiliated Hospital of Guangxi University of Chinese Medicine (about 200 breast cancer patients seen annually), and Liuzhou Maternity and Child Health Care Hospital (about 120 breast cancer patients seen annually). A fixed quota (number of participants recruited) will be distributed to each center based on their total number of breast cancer patients yearly (Additional file 1). The recruitment would start from December, 2016, and will end in October, 2019 synchronously in the three centers. For patients assigned to the real acupuncture group, a standard acupuncture procedure using the real will be performed; for patients assigned to the sham acupuncture group, a standard acupuncture procedure using the sham needles will be performed. The acupoints, frequency (3 times a week for 4 weeks), and duration (30 min after de qi) of each patient in both groups should be the same. All participants in both groups will receive the same usual care of decongestive therapy following acupuncture. An overview of the enrollment procedures, the study design, and the assessments of this trial is illustrated in Table 1.

**Table 1 Tab1:**
[figure not shown]
Procedures and time-points of enrollment, intervention, and assessment in this trial

This study has been approved by the Institutional Review Board of the Fourth Affiliated Hospital of Guangxi Medical University (Approval Number: PJK2016090).

### Study oversight

Three committees will be in charge of the supervision in this trial.The trial steering committee (TSC).

The TSC, composed of trial designers of the trial and coordinators of each center, is responsible for key technical and operational problems, such as changes in eligibility criteria, outcomes, analyses, etc. A meeting will be held every month.2.The trial coordinating committee (TCC)

The TCC, composed of coordinators, acupuncturists and nurses in each center, is in charge of specific business, such as recruitment and identification of possible participants, information dissemination of this trial, collection and preservation of data and reports, and management of trial sites. The coordinators in each center are responsible for the establishment of the standard operation procedures and the training of relevant staff prior to the initiation of this trial. The TCC will cooperate with TSC and make a report every month.3.The data and safety monitoring board (DSMB)

The DSMB, composed of experienced experts in experimental design and statistics, is responsible for review and evaluation of the trial periodically. They mainly focus on issues such as execution of the trial, collection of the data, participants’ safety, and personal privacy protection. They will also report to the TSC monthly and may provide advice in the modification or termination of the trial.

### Eligibility criteria

In this trial, following inclusion criteria will be adopted:▪ women who have completed breast cancer treatment for more than 1 year;▪ no evidence of recurrence;▪ unilateral lymphedema resulting from surgery for breast cancer;▪ age between 20 and 45;▪ BMI between 18 and 25;▪ mild to moderate lymphedema (10% to 40% increase in volume compared to the unaffected arm).Patients will be excluded as follows:▪ bilateral lymphedema;▪ current use of chemotherapy or radiotherapy;▪ history of bilateral axillary lymph node dissection;▪ serious lymphedema, >40% increase in volume compared to the unaffected arm;▪ pregnant women or overweight women;▪ unable to adhere to the protocol or the treatment schedule;▪ recurrent breast cancer or evidence of other active cancer;▪ current use of diuretics like Diosmin, or other investigational drugs;▪ contraindications for acupuncture, such as infections, open wounds, or broken skin.

### Forbidden drugs and concomitant treatments

To avoid cross effect, following drugs are unacceptable in this trial, including Diosmin, Hesperidin, and diuretics. Other concomitant treatments should be consulted with the physician in charge and meticulously recorded.

### Recruitment of participants

The nurses in each center will identify possible participants according to the inclusion and exclusion criteria. Then possible participants will be invited to attend a screening visit, during which a routine physical examination and a baseline assessment including the upper limbs and risks of recurrence will be performed. The coordinators in charge will confirm their eligibility based on their health status and inclusion criteria. For every eligible participant, a unique number will be given by the coordinators based on their enrollment sequence after a written informed consent was obtained, and data on demographic information will be collected through interviews and questionnaires by the acupuncturists funded by this project.

### Randomization and allocation

Eligible participants in each center are randomized into the real acupuncture group and the sham-acupuncture group at a ratio of 1:1 according to the randomization sequence, which is a series of randomization numbers representing each patient’s unique number, and pre-generated by the chief designer using RAND function in Microsoft Excel program according to the quota of each center (Additional file 1).

### Blinding

In this trial, participants and statisticians are blinded to the group assignment, whereas acupuncturists are not, due to the nature of this trial. However, to minimize the unintentional physical cues and bias in this trial, acupuncturists will be required to emulate the same procedure for the sham-acupuncture groups. And the credibility of blinding will be assessed by experiments before the formal trial, and adjustments will be made until it is acceptable. The process of the blinding will be monitored and assessed by the DSMB.

### Intervention

Eligible participants will be required to set up an appointment by the acupuncturist according to their symptoms patterns, such as the time period their lymphedema manifest the most typical symptoms. Upon arrival at scheduled appointments, participants will receive real or sham acupuncture accordingly on both arms. In this trial, we apply sterilized stainless steel needles (0.25 × 40 mm; Asia Med, Munich, Germany) in real acupuncture group, and blunt telescopic placebo needles (Streitberger needle; Asia Med, Munich, Germany) in sham-controlled group. All procedures will be performed by officially registered acupuncturists with clinical experience of 3 years at least.

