### Decongestive therapy

For ethical considerations (the interest of participants in sham-group), every participant in both groups will receive the same usual care of decongestive therapy after treatment, which includes a daily manual lymph drainage, gentle exercise, applying moisturizer, and wearing elastic compression garments. Table 2 details the duration, frequency, executor, and location of each step. For participants who take other practice, detailed reports will be required.

**Table 2 Tab2:** Overview of standard decongestive therapy contents

Standard decongestive therapy	Duration	Frequency	Location	Record	Note
Manual Lymph Drainage	30 min	Daily	Hospital	Massage Therapist	Meticulous records are needed otherwise.
Applying Moisturizer	3 times	Daily	Home	Participant	
Gentle Exercise	2 h	Daily	Home	Participant	
Wearing Compression Garment	3 h	Daily	Home	Participant	

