### Data collection

Before the first treatment session, every participant will get an assessment of both limbs by perometer, which is an automated infrared light digital scanner equipped with a microcomputer. When the limb is placed inside, the infrared light transmitters located on two sides of the perometer will be activated, and the blockage of the transmission of infrared light from both sides caused by the limb will be recorded and calculated. As the transmitters move along the limb, a series of images will be recorded. Hence a highly accurate measurement of the limb size and volume will be created. And these results will serve as the baseline data. Following the treatment of each session, participants in both groups will be asked to take assessments to get the interim data. Upon the last session, the assessments of both limbs will be adopted as the end-point data. For each arm, the measurement will repeat 3 times to ensure the reliability. Table 1 illustrates all the time points when measurements are taken during the whole procedure.

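### Baseline volume is read before the first session and the endpoint after the last, at visit times set by the unblinded acupuncturist, so a lasting reduction is not isolated and uneven timing is not prevented

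*Protocol article*

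**What the plan says.** All references are to the protocol article.

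- **Visit times (Intervention).** Participants are to "set up an appointment by the acupuncturist according to their symptoms patterns, such as the time period their lymphedema manifest the most typical symptoms".
- **Who knows the arm (Blinding).** "participants and statisticians are blinded to the group assignment, whereas acupuncturists are not".
- **Baseline (Data collection).** "Before the first treatment session, every participant will get an assessment of both limbs by perometer". Recruitment of participants also places a limb assessment at the screening visit, where "a baseline assessment including the upper limbs and risks of recurrence will be performed".
- **Session readings.** The abstract says "Volume measurements of both arms will be performed for every participant after each treatment", and Data collection says "Following the treatment of each session, participants in both groups will be asked to take assessments to get the interim data".
- **Endpoint (Data collection).** "Upon the last session, the assessments of both limbs will be adopted as the end-point data". Read with the two sentences on session readings, this is a reading after needling. The text names no volume reading later than the last session; Table 1, which lists the time points, is not shown.
- **Same-day co-treatment (Decongestive therapy).** Both groups receive "the same usual care of decongestive therapy after treatment", including 30 minutes of daily manual lymph drainage in hospital. The visible text does not place the volume reading before or after it.

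**The concern.** The primary outcome (ARLVR) is a change between two readings taken under different conditions: one before any needling, the other just after a session. The Background section describes the condition as chronic swelling that often needs lifetime management, so the reduction of interest is a lasting one. Sham needles do not penetrate the skin. If penetrating needling causes a brief change in arm volume, it would appear in the real group at the endpoint and be counted with any lasting benefit.

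The scheduling rule adds a second weakness. Booking by symptom pattern presupposes that symptoms vary over time, and the person who books knows the allocation. Randomisation does not protect a visit time chosen after allocation by someone unblinded. The safeguard under Blinding concerns imitation of the needling procedure, not scheduling. The Discussion credits the index with removing base effect and weight fluctuation, but does not mention time of day.

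At stake are what a positive result would mean and, if timing differed between groups or was erratic, the accuracy and precision of the estimate.

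**Working it through.** **Inputs**

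- ARLVR mean and SD: 0.32 and 0.25 (real), 0.22 and 0.20 (sham); alpha 0.05, beta 0.2; 164 required, 200 planned, 100 per arm (Sample size calculation).
- Eligible excess volume: e = 10% to 40% of the unaffected arm (Eligibility criteria).
- Day-to-day variability of limb volume: 0.5, no unit given (Discussion).
- ARLVR is taken by its verbal definition, that is, reduction divided by baseline excess volume.

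**Step 1. Reproduce the plan's figure.**
Pooled SD = sqrt((0.25² + 0.20²)/2) = 0.2264. Effect size = 0.10/0.2264 = 0.4417, as stated. A two-sided t test at 0.05 with 80% power needs 81.4, so 82 per arm, or 164 in total, as stated. With 100 per arm, power is 87.5%.

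**Step 2. Express the planned effect as arm volume.**
With the unaffected arm set to 1, the affected arm is 1 + e and the excess is e. A difference of 0.10 in ARLVR is 0.10·e of volume, or 0.10·e/(1 + e) of the affected arm.

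| Excess e | 10 points, as % of affected arm | ARLVR points from a 0.5% shift | ARLVR points from a 1% shift |
|---|---|---|---|
| 10% | 0.9% | 5.5 | 11 |
| 25% | 2.0% | 2.5 | 5 |
| 40% | 2.9% | 1.75 | 3.5 |

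The last two columns are s(1 + e)/e for a shift s in the affected arm alone. Reading the unitless 0.5 as 0.5% is an assumption.

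**Step 3. Effect of timing noise on power (assumed noise).**
Take independent noise s in the affected arm at each of two readings, with e = 25% and the denominator held fixed. The added SD is sqrt(2)·s·(1.25/0.25). The total SD is sqrt(0.2264² + added SD²).

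| Noise per reading | Added SD | Total SD | Effect size | Power, 100 per arm |
|---|---|---|---|---|
| 0 | 0 | 0.2264 | 0.442 | 87.5% |
| 0.5% | 0.035 | 0.2291 | 0.436 | 86.7% |
| 1% | 0.071 | 0.2372 | 0.422 | 84.3% |
| 2% | 0.141 | 0.2669 | 0.375 | 75.1% |

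**Step 4. What if a shift did differ between groups?**
Suppose there is no lasting effect, but a brief or timing-related between-group shift b in ARLVR. The standard error is 0.2264·sqrt(2/100) = 0.0320. By the normal approximation, the chance of a significant result is 5.0% at b = 0, 9.6% at 0.02, 15.5% at 0.03 and 34.5% at 0.05. These values of b are illustrations; the documents supply none.

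**The case against.** The strongest reply is that the design is symmetric. Symptom-based booking, the order of readings, acupoints, frequency, duration and decongestive therapy are the same in both groups, so whatever they do to volume in common cancels in the real-versus-sham difference. This stands. A reader might infer from the unblinded scheduler and the before/after readings that the primary comparison is biased. The documents do not support that: they permit different scheduling by group but do not state or imply it. Booking by a participant's own pattern, if the pattern is stable, could even place her visits at similar times.

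A reader might also take the scheduling rule to mean visits at peak symptoms. The text does not say so; it mentions typical symptoms, and only as an example.

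A brief effect of real over sham needling is a genuine effect at that moment. It is therefore a question of what the estimate means, not of confounding. This also stands. In addition, both arms of the body are needled and the unaffected arm's change is subtracted, so a response common to both limbs is offset. Only a response specific to the swollen arm would remain.

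On size, the planning SDs rest partly on preliminary clinical data and may already contain some timing variation. Noise of 1% to 2% is two to four times the only figure given, if that figure is a percentage; at 0.5%, power hardly moves.

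Finally, clock times and the order of steps within a visit may be in Table 1 or in operating procedures not shown. Their absence from the article is therefore not the point. The point is what the article does fix: a pre-session baseline, a post-session endpoint, and booking by an unblinded person.

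None of this provides a reading that separates a lasting change from an immediate one, or a barrier to uneven timing.

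**Conclusion.** The point holds as a weakness of measurement design, not as a demonstrated bias. As described, the ARLVR measures the immediate and cumulative effects of 12 sessions together, and a lasting reduction of a chronic swelling cannot be isolated from it. Visit timing is open to the judgement of someone who knows the arm, and no stated rule matches the endpoint reading to the baseline reading in time of day.

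The documents give no size for a brief needling response or for a timing effect, so the figures are sensitivities only. They show that the planned effect is small in volume terms (about 0.9% to 2.9% of the affected arm), so small shifts in volume matter. Assumed noise of 1% to 2% per reading at 25% excess would cost roughly 3 to 12 percentage points of power with 100 per arm. These results assume the verbal definition of ARLVR, shifts confined to the affected arm, independent noise at the two readings, and planning SDs that do not already include that noise. The matter is worth correcting because the correction is cheap.

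**What to change.** 1. Take the baseline and last-visit perometer readings at the same clock time, within about 1 hour for each participant.
2. Have both readings booked before randomisation, by existing staff who do not know the arm, and not by the treating acupuncturist.
3. At the last visit, add a reading before needling and before that day's lymph drainage. Use this like-for-like reading with the pre-session baseline for the ARLVR.
4. Keep the post-session reading and report it as supportive, described as an immediate post-session result.

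The cost is less flexible appointments and one extra set of readings at a visit that already takes place. The primary outcome would also leave out the immediate effect of the last session, which the supportive reading would still show. Treatment itself is unchanged.

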### Real acupuncture group

Patients in the real acupuncture group will receive true acupuncture 3 times a week for 4 weeks (12 sessions) at 6 acupoints in each arm: Jianyu (LI 15), Jianliao (SJ 14), Binao (LI 14), Quchi (LI 11), Shousanli (LI 10), and Waiguan (SJ 5). These acupuncture points were selected on the basis of classic TCM record, the published literature [30–35], and the consensus between our experienced acupuncturists. Acupoints are detailed in Fig. 1. After the application of alcohol swabs, these acupoints will be covered by adhesive plaster with plastic rings, and stimulated by manual rotation of the needles accompanied by lifting and thrusting gently to make patients get de qi, which is a sensation of aching or distension or numbness elicited by acupoint stimulation [36, 37]. Then needles will stay put for 30 min.

**Fig. 1 Fig1:**
[figure not shown]
Overview of selected acupoints in this trial. Participants will receive real acupuncture or sham-acupuncture at the same acupoints in both arms 3 times a week for 4 weeks (12 sessions)

